## Abstract

**Background:**

Fundal pressure (pushing on the upper part of the uterus in the direction of the birth canal) is often performed in routine practice, however the benefit and indications for its use are unclear and vigorous pressure is potentially harmful. There is some evidence that it may be applied routinely or to expedite delivery in some situations (e.g. fetal distress or maternal exhaustion), particularly in settings where other methods of achieving delivery (forceps, vacuum) are not available. Gentle assisted pushing (GAP) is an innovative method of applying gentle but steady pressure to the uterine fundus with the woman in an upright posture. This trial aims to evaluate the use of GAP in an upright posture, or upright posture alone, on reducing the mean time of delivery and the associated maternal and neonatal complications in women not having delivered following 15-30 min in the second stage of labour.

**Methods/Design:**

We will conduct a multicentre, randomized, unblinded, controlled trial with three parallel arms (1:1:1). 1,145 women will be randomized at three hospitals in South Africa. Women will be eligible for inclusion if they are ≥18 years old, nulliparous, gestational age ≥ 35 weeks, have a singleton pregnancy in cephalic presentation and vaginal delivery anticipated. Women with chronic medical conditions or obstetric complications are not eligible. If eligible women are undelivered following 15-30 min in the second stage of labour, they will be randomly assigned to: 1) GAP in the upright posture, 2) upright posture only and 3) routine practice (recumbent/supine posture). The primary outcome is the mean time from randomization to complete delivery. Secondary outcomes include operative delivery, adverse neonatal outcomes, maternal adverse events and discomfort.

**Discussion:**

This trial will establish whether upright posture and/or a controlled method of applying fundal pressure (GAP) can improve labour outcomes for women and their babies. If fundal pressure is found to have a measurable beneficial effect, this gentle approach can be promoted as a replacement for the uncontrolled methods currently in use. If it is not found to be useful, fundal pressure can be discouraged.

## Background

The first stage of labour is the period of time from the onset of intense, synchronous and co-ordinated contractions leading to full cervical dilatation. The second stage of labour is the period from full cervical dilatation to expulsion of the baby through the vagina. UK guidelines define the normal duration of the second stage of labour to be about 0.5 to 2.5 h for nulliparous women, and up to 2 h in parous women following the onset of the active second stage of labour [1]. There is little consensus as to what constitutes a prolonged second stage of labour. UK guidelines define it as more than two hours and one hour of the onset of the active second stage for nulliparous and parous women, respectively [1]. After this time, women in the UK are referred for operative vaginal birth. Poor contractions, maternal exhaustion, epidural analgesia and occipito-posterior fetal positions are common causes of prolonged second stage. These causes can be difficult to overcome without interventions such as oxytocin (to stimulate or augment uterine contractions) and assisted vaginal birth (such as forceps or vacuum).

Fundal pressure involves the application of pressure by the birth attendant to the uppermost part of a woman’s uterus, directed towards the birth canal, in an attempt to assist spontaneous vaginal delivery [2]. Applying manual fundal pressure was originally described by Samuel Kristeller in the 1870s and was known as the Kristeller manoeuvre. Nowadays, although this manoeuvre is not officially taught to midwives and doctors, the use of manual fundal pressure is still performed in clinical practice, although often not documented in clinical records [3]. Applying fundal pressure under controlled conditions has been shown to increase intrauterine pressure [4]. This increase in the expulsive uterine forces could potentially assist the mother to push the baby out. There is evidence to show that fundal pressure is used in formal and informal childbirth practice, in developed and less developed countries [5–8]. However, how frequently fundal pressure is performed in routine practice and the indications for its’ use in different settings is unclear. In a 2006 postpartum survey of women in the USA, it was reported that there was a ‘notable minority’ of births during which ‘a staff member pressed on the mother's belly to help push the baby out’ [7]. A survey in the Netherlands between 1994 and 1995 reported a prevalence of 4 % [8]. Two other studies in tertiary care institutions have reported the incidence of fundal pressure application to be 23-24 % [9, 10]. It may be applied routinely, in prolonged second stage of labour, for situations where delivery needs to be expedited (e.g. fetal distress) or for maternal medical conditions where prolonged pushing is contraindicated [2]. Fundal pressure is also used routinely to assist birth at Caesarean section.

The safety of this intervention has not been established [3, 11–13], and its use remains controversial [13]. Applying fundal pressure has been both recommended and condemned as a strategy for assisting birth in the management of shoulder dystocia [14, 15]. To our knowledge, the only published randomized controlled trials (RCTs) of manual fundal pressure during vaginal birth have found no benefits associated with its use, but the numbers studied were small [16, 30]. A pilot RCT of manual fundal pressure compared with standard care in 209 nulliparous women with uncomplicated pregnancies in a hospital in India found no significant reduction in the duration of the second stage of labour, but an increase in perineal injuries [16]. A 2005 review of the manoeuvre concluded that the role of fundal pressure is understudied and caution should be exercised until it is proven to be safe and effective [11]. A 2009 Cochrane review concluded that there is currently insufficient high quality evidence to draw firm conclusions about the benefits and risks of this practice [2].

Fundal pressure is usually applied manually; however, two small RCTs (conducted in hospitals in South Korea and Italy) have evaluated fundal pressure applied using two different types of inflatable belts compared with standard care in nulliparous women with uncomplicated singleton pregnancies [17, 18]. These studies reported a significant reduction in the duration of the second stage of labour and, in the study in Italy, a significant reduction in perineal trauma, CS, vacuum delivery and neonatal ICU admission.

### Potential benefits and risks of fundal pressure

In well-resourced settings, a prolonged second stage of labour is usually overcome by assisted vaginal delivery or caesarean section. In lower-income countries, for the majority of births, instrumental or operative delivery methods may not be available; and timely transfer to a service with these facilities may not be feasible. In these settings, fundal pressure may be an effective way of expediting the birth of a baby, and potentially reducing the risk of neonatal morbidity and mortality associated with a prolonged and difficult birth. In addition, this intervention may be valuable for women in whom instrumental delivery is contraindicated (such as HIV infection) and for whom assistance in the second stage of labour is necessary. However, even in settings where instrumental or operative delivery is available, fundal pressure may reduce the need for their use and, thereby, reduce the risk of associated third-degree tears or surgery. The potential benefits, therefore, have implications for obstetric care at all levels.

Fundal pressure manoeuvres of variable force and direction are commonly used by birth attendants with potentially harmful effects. Maternal complications ascribed to these ‘conventional’ fundal pressure manoeuvres include perineal tears, uterine rupture, uterine inversion, pain, hypotension, respiratory distress, abdominal bruising, fractured ribs, and liver rupture [19–26]. Excessive fundal pressure has also been cited as a predisposing factor for amniotic fluid embolism [27]. In the neonate, fundal pressure has been implicated as a possible cause of fractures and brain damage [28, 29]. The theoretical basis for the latter is that applying mechanical forces to the uterus to increase intrauterine pressure could cause a concomitant increase in fetal intracranial pressure. This, in turn, could lead to a decrease in fetal cerebral blood flow and subsequent cerebral handicap in the infant. The same mechanism has been postulated to occur in cases of cerebral palsy following uterine tetany or forceps delivery. In addition, if used in the presence of cephalo-pelvic disproportion, the risk of maternal and neonatal injury would be high.

There is also a theoretical possibility that fundal pressure may cause maternal-fetal transfusion of blood, increasing the risk of viral transmission such as HIV. However, in a randomized trial of fundal pressure versus no fundal pressure at caesarean section, no evidence of maternal-fetal transfusion was found [30].

The lack of a standardised method of application is also contributing to differences of opinion regarding the utility of fundal pressure. Although it has been described as being ‘applied gently with one hand on the uterine fundus at a 30° to 45° angle to the maternal spine in the direction of the pelvis’ [13], in a longitudinal direction, it is difficult to quantify or control the amount of force used. Fundal pressure may vary from the gentle pressure described above, to vigorous force applied with both hands or elbows using the attendant’s whole weight. A tendency to use rapid thrusting movements may cause sharp rises in intrauterine pressure and increase the risk of maternal and neonatal injury. The gentle assisted pushing (GAP) method described in this protocol is designed to eliminate the possibility of excessive use of force, by positioning the attendant behind the women who is in an upright position, so that only the pressure applied with her hands can be used.

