### Study participants

All women attending participating hospitals for delivery (who meet the inclusion criteria) during the study period will be approached for participation in this study.

The eligibility criteria are:Equal to or greater than 18 years old;Nulliparous women;Gestational age ≥ 35 weeks;Singleton pregnancy;Vaginal delivery anticipated;Cephalic fetal presentation;Baby’s heartbeat detected;No chronic medical conditions, including heart disease, epilepsy, hypertension, diabetes mellitus and renal disease;No obstetric complications, including hypertensive disorders of pregnancy, cephalo-pelvic disproportion, antepartum haemorrhage, intra-uterine growth restriction, fetal distress, intra-amniotic infection; andWilling and able to provide consent

Women whose labours are induced or augmented, or women with HIV, are not excluded from this trial. However, this information will be captured in the trial forms.

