#### Arm 3: Routine practice (recumbent/supine posture only)

The current posture as practiced in the participating sites will be used.

In all intervention arms, the trained birth attendant encourages the women to bear down. All other delivery procedures, such as fetal heart monitoring and routine oxytocin after the birth, are performed according to the usual hospital routine and will not differ between the groups.

For Arm 3 (routine practice), if the woman remains undelivered 30 min after randomization, fundal pressure or changes in posture may be considered necessary by the birth attendant according to routine local practice. Additional procedures or treatments performed at the discretion of the attendant will then be recorded in the study form.

At any stage of the labour, routine procedures such as change in posture, oxytocin administration, forceps or vacuum delivery or caesarean section will be available as considered indicated by the responsible clinician. If forceps, vacuum delivery or caesarean section is required, GAP and/or upright only posture will be stopped.

Electronic fetal heart rate monitoring is not routinely used in the study institutions in uncomplicated pregnancies; therefore, this equipment is unlikely to interfere with the administration of the interventions in this study. Auscultation of the fetal heart rate will be performed after each contraction following randomization. If electronic monitoring is considered necessary by the birth attendant, the GAP procedure will not interfere with monitoring as the monitor is positioned on the anterior aspect of the uterus while pressure is applied to the fundal aspect.

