### Study outcomes

The primary outcome is defined as mean time (minutes) from randomization to delivery.

Secondary outcomes include the following:Delivery outcomes:oNo spontaneous delivery within 15 min of randomization;oOperative delivery (vacuum, forceps or caesarean section); andoEpisiotomy or 2nd/3rd degree tears.Neonatal outcomes: oCord blood pH < 7.2;o5-min Apgar score <7;oNeonatal injury;oNeonatal encephalopathy;oAdmission to neonatal high care nursery for ≥24 h; andoNeonatal death.

Mothers will also be asked to grade their discomfort experienced during the second stage of labour. All adverse events and serious adverse events will also be recorded.

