### Adverse events

An adverse event is any untoward medical occurrence in a patient or clinical investigation subject and which does not necessarily have a causal relationship with this treatment. An adverse event can therefore be any unfavourable and unintended sign (including an abnormal laboratory finding), symptom, or disease temporally associated with the use of a medicinal (investigational) product, whether or not related to the medicinal (investigational) product.

Any adverse event that requires treatment will be reported an Adverse Event (AE) form and the principal investigator immediately alerted.

The serious adverse event form will be completed in the following circumstances:The woman has been transferred to another department or hospital in relation to an adverse event after enrolment in the trial.An adverse event has caused prolonged hospital stay.The woman has been re-admitted to the hospital for further care of an adverse event that has occurred while she was in the trial.The adverse event has caused permanent loss of function of a system or organ.The adverse event is considered to be life threatening.The adverse event has resulted in death.

Reporting of AEs and SAEs will be done using an adverse event (AE) form and serious adverse event (SAE) form. These forms will be completed by data collectors and the principal investigator informed as soon as possible. The WHO project manager will be notified of the AE or SAE within 24 h, and the DSMC will be notified of SAEs within 24 h (accelerated reporting).

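### Neonatal death is the only mortality outcome listed, so a fetal death between randomization and birth falls outside the pre-specified mortality comparison

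*Protocol article*

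**What the plan says.** Under Study participants in the protocol article, one eligibility criterion is "Baby’s heartbeat detected". The excluded obstetric complications include "intra-uterine growth restriction, fetal distress, intra-amniotic infection". Sampling and allocation then limits randomization to recruited women who reach the second stage without major complications.

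Under Study outcomes, the neonatal list has six items: cord blood pH below 7.2, 5-minute Apgar below 7, injury, encephalopathy, a stay of 24 h or more in the high care nursery, and neonatal death. Stillbirth, fetal death, intrapartum death and perinatal death are named nowhere in the article, and neonatal death is not defined to include any of them.

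The same section adds that "All adverse events and serious adverse events will also be recorded". Under Adverse events, one criterion for a serious event is "The adverse event has resulted in death", and "the DSMC will be notified of SAEs within 24 h". Data analysis says that categorical outcomes will be compared as risk ratios with 95 % confidence intervals, using subjects with outcome data available.

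The Background section on benefits and risks gives the mortality rationale: "potentially reducing the risk of neonatal morbidity and mortality associated with a prolonged and difficult birth". It also describes a possible harm that acts before birth, through raised fetal intracranial pressure and reduced fetal cerebral blood flow.

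**The concern.** The trial tries to shorten the interval from randomization to birth. The benefit argued for, and part of the harm feared, both act within that interval, yet the mortality outcome starts only once a baby is born alive. Live birth is itself a post-randomization event that the intervention may influence, so an outcome confined to live-born babies is no longer a comparison of everyone randomized.

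The distortion can run either way. A death in labour that the intervention prevents is not credited, and one that it causes is not counted. Encephalopathy and nursery admission share the problem, because a stillborn baby cannot have either event. The 5-minute Apgar outcome could register a stillbirth, but only if a score of 0 is entered, and the article does not say whether it would be.

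**Working it through.** **The outcome list against the time line**

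1. At screening, a fetal heartbeat is required. At randomization, the woman must have no major complication. I take this to mean that every fetus is meant to be alive when allocated.
2. From randomization to birth, a death is a post-randomization event. It fits the wording of the serious adverse event criterion on death. It does not fit neonatal death.
3. From birth to discharge, a death is a neonatal death, and follow-up to discharge is planned under Follow-up procedures.

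The gap is the second period only.

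**Expected number of events**

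The documents give no intrapartum death rate, so there is no planned figure to reproduce for this outcome. The denominator does reproduce: 347 × 3 = 1,041 and 1,041 × 1.1 = 1,145.1, stated as 1,145; per arm 347 × 1.1 = 381.7, stated as 382.

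With an assumed rate r, the expected count is 1,145 × r and the chance of at least one event is 1 − (1 − r)^1145.

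| Assumed r per 1,000 | Expected, all arms | Expected per arm of 382 | Chance of at least one |
|---|---|---|---|
| 1 | 1.1 | 0.4 | 68 % |
| 2 | 2.3 | 0.8 | 90 % |
| 5 | 5.7 | 1.9 | over 99 % |

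**How the comparison can mislead**

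These counts are assumed. Take two arms of 382. The control arm has 2 intrapartum deaths (2/382 = 5.2 per 1,000, about the top of the range above) and 1 neonatal death. The intervention arm would have had the same, except as stated.

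| Effect of the intervention | Neonatal deaths, control vs intervention | Fetal plus neonatal deaths, control vs intervention |
|---|---|---|
| One stillbirth becomes a live birth; baby survives | 1 vs 1 (benefit unseen) | 3 vs 2 (benefit seen) |
| One stillbirth becomes a live birth; baby dies before discharge | 1 vs 2 (apparent harm) | 3 vs 3 (neutral) |
| One extra intrapartum death | 1 vs 1 (harm unseen) | 3 vs 4 (harm seen) |

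Apparent harm arises only in the second row. In the first row, the surviving baby could still add an encephalopathy or admission event that a stillborn baby could not have.

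**Precision**

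For 2 vs 1 deaths the risk ratio is 2.0. The standard error of its logarithm is √(1/2 + 1/1 − 2/382) = 1.22, so the 95 % interval runs from about 2.0/e^(1.96 × 1.22) = 0.2 to 2.0 × e^(1.96 × 1.22) = 22. Neither definition would give a conclusive result at these counts. The gain is a correct tabulation, not power.

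**The case against.** The strongest reply is that the deaths are not lost. All serious adverse events are recorded, the criterion on death is not limited to the mother, and the monitoring committee hears within 24 h and can recommend stopping an arm. A reader might infer from the outcome list that a fetal death is a non-event in this trial. The documents do not support that: it is absent from the mortality outcome, but it is reportable as a serious adverse event and could count as a low Apgar. What remains is that individual reports do not supply the pre-specified risk ratio that Data analysis promises.

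A reader might also infer that turning a stillbirth into a live birth would count as harm. It could, but only if that baby then dies before discharge; otherwise the benefit is simply not seen. Nor can a dramatic reversal be claimed. An example with 4 intrapartum deaths in one arm needs 4/382 = 10.5 per 1,000, more than twice the top of the range assumed here.

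The list is introduced as including its items, so it is not worded as exhaustive, and the case report forms and analysis plan are not shown. How a stillborn baby enters each denominator may be settled there. That is fair for scoring detail. It is weaker for the mortality outcome, which the article itself names and which a reader would take as the planned comparison.

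Events should be few. Fetal distress and growth restriction are excluded, "Auscultation of the fetal heart rate will be performed after each contraction following randomization", operative delivery is available, and the planning means are about 19 to 23 min. This limits the weight of the point.

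Finally, a baby who is admitted and dies before 24 h misses the admission outcome but is still counted under neonatal death, so that loss is not hidden.

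**Conclusion.** The point holds in a limited form. As listed, the mortality outcome is conditional on live birth and omits deaths in the very interval that the intervention aims to shorten. This rests on the ordinary meaning of neonatal death and on every fetus being alive at randomization, as the eligibility and allocation rules intend.

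The size is small in absolute terms: about 1 to 6 intrapartum deaths in the whole trial at an assumed 1 to 5 per 1,000. With counts that low, one or two deaths left out can change the apparent direction, though not establish an effect. This is a secondary safety outcome. The primary outcome, the sample size and the reporting of individual serious events are unaffected.

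**What to change.** Under Study outcomes, replace neonatal death with *fetal death after randomization or death of the baby before discharge*. Use all randomized women as the denominator, apart from those who withdraw consent, whom Data analysis already excludes. Report the two components separately as well. State that a stillbirth counts as an event for 5-minute Apgar below 7.

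Adding death to the nursery admission outcome is optional, since early deaths are already counted elsewhere on the list.

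The cost is a change of wording. Delivery details and follow-up to discharge are already collected, and deaths are already reportable. No extra women, visits or procedures are needed.

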### Statistical methods

The sample size has been calculated to be powered to detect a reduction in the primary outcome of mean time (minutes) from randomization to delivery of > =3 min. A reduction of > =3 min was used due to the findings of the study by Api et al (2009) [31], that reported a time from randomization to delivery of 23.1 min (SD 12.2 min) in the control group (*N* = 56), and 18.6 min (SD 9.5 min) in the fundal pressure group (*N* = 34). We assumed that upright posture alone would likely lie between these two (i.e. approximately 20.0 min). Using the Bonferroni rule to control for multiplicity, alpha is divided by the number of comparisons (0.05/3 ≈ 0.02). We assumed a power of 90 % and alpha of 95 %. The study therefore requires 347 women in each arm, i.e. 1,041 women for all three arms. To allow for 10 % non-compliance, we aim to recruit 382 in each arm. The final sample size for the whole study is 1,145 women.

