### Data analysis

Data will be generated from the on-line data management system and analysed in SPSS. The primary analysis will be based on all subjects with outcome data available. Any participants with protocol violations, including women who no longer wish to receive their allocated intervention but are prepared to have data collected, will be analysed in the group to which they were allocated (intention-to-treat). Data from subjects who withdraw their consent will be excluded from the analysis and considered as lost to follow-up.

Baseline characteristics will be compared between groups to confirm the effectiveness of the randomization process in creating similar groups. Numbers and baseline characteristics of women lost to follow-up will also be compared between study groups to detect any imbalances.

Most study outcomes are categorical variables. For these types of variables, the number of subjects, number of missing values and percentages will be reported. Categorical variables will be compared between study arms as risk ratios with 95 % confidence intervals.

For continuous variables, e.g. time to delivery, the number of subjects, and number of missing values, minimum, maximum, means and standard deviations will be reported. Appropriate transformation of non-normal or skewed measurement will be performed. Means will be compared using t-tests for two independent samples, and 95 % confidence intervals will be calculated. If transformations do not generate a distribution approaching normality, medians and interquartile range (IQR) will be reported. The primary outcome of the study is “mean time (minutes) from randomization to delivery”. The survival technique log-rank test will also be used to compare the survival rates of the three groups, pairwise. Results will be reported according to CONSORT guidelines [22].

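### Cord blood pH is analysed only as below or not below 7.2; adding a comparison of the measured values would sharpen a secondary neonatal safety outcome at little cost

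*Protocol article*

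**What the plan says.** The protocol article, under Potential benefits and risks of fundal pressure, explains how fetal brain damage might arise: "applying mechanical forces to the uterus to increase intrauterine pressure could cause a concomitant increase in fetal intracranial pressure". It goes on to reduced cerebral blood flow and later handicap. It does not mention pH.

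The Study outcomes section lists six neonatal outcomes, all secondary: cord blood pH below 7.2, 5-minute Apgar below 7, injury, encephalopathy, a stay of at least 24 hours in the high care nursery, and death. Cord pH appears only in its dichotomised form.

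The Data analysis section has two rules. For binary outcomes: "Categorical variables will be compared between study arms as risk ratios with 95 % confidence intervals". For measured ones: "For continuous variables, e.g. time to delivery, the number of subjects, and number of missing values, minimum, maximum, means and standard deviations will be reported", followed by transformation where needed, t-tests and 95% intervals. Time to delivery is the only example named under the second rule. The sample size rests on time to delivery alone; no precision or power is stated for any neonatal outcome.

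**The concern.** A pH is a measured number. Reducing it to one side of 7.2 treats 7.19 and 6.95 alike, and 7.21 and 7.35 alike. If the intervention moves pH by degrees, that discards information the trial could use.

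This matters more here than for a typical secondary outcome. Staff know the allocation, and Apgar, injury, encephalopathy and nursery admission all involve some judgement. Death does not, but it should be very rare in women selected for low risk. Cord pH is thus the neonatal outcome least exposed to unblinded assessment and still likely to be informative. The Discussion says that GAP could be promoted if it proves beneficial, so an unnecessarily wide interval on a neonatal safety outcome has a practical cost.

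**Working it through.** **1. Number per arm.** The protocol's figure is for the primary outcome and is used here only to fix n. The inputs, from Statistical methods, are a difference in "mean time (minutes) from randomization to delivery of > =3 min", "23.1 min (SD 12.2 min) in the control group", "18.6 min (SD 9.5 min) in the fundal pressure group", power 90%, and alpha 0.05/3 rounded to 0.02.

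- Average SD = sqrt((12.2² + 9.5²)/2) = 10.93.
- n = 2 × (2.326 + 1.282)² × 10.93² / 3² ≈ 346 per arm, or 347.2 with the t distribution. The stated 347 is reproduced.
- 347 × 1.10 = 381.7, the stated 382.

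Nothing in this calculation bears on pH.

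**2. Information kept by a cut.** Assume pH is normal and every baby's value shifts by the same small amount. If a share p lies below the cut, the proportion keeps φ(z_p)² / [p(1 − p)] of the information in the mean. Because p is not given, a range is shown.

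| Assumed share below 7.2 | Kept | Lost |
|---|---|---|
| 5% | 22% | 78% |
| 10% | 34% | 66% |
| 15% | 43% | 57% |
| 20% | 49% | 51% |
| 25% | 54% | 46% |
| 50% (best case) | 64% | 36% |

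**3. Power, uniform shift.** Assumptions, none from the protocol: control mean 7.27, SD 0.08, a drop of 0.02 in every baby, complete cord samples in 382 per arm, two-sided 5% (matching a 95% interval).

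- Control share below 7.2: Φ(−0.07/0.08) = Φ(−0.875) = 0.191. With the drop: Φ(−0.05/0.08) = Φ(−0.625) = 0.266.
- Proportions: SE = sqrt((0.191×0.809 + 0.266×0.734)/382) = 0.0303; 0.0752/0.0303 = 2.48; power = Φ(2.48 − 1.96) ≈ 70%.
- Means: SE = 0.08 × sqrt(2/382) = 0.00579; 0.02/0.00579 = 3.46; power = Φ(3.46 − 1.96) ≈ 93%.
- With a drop of 0.015 the powers are about 45% and 74%. With 347 per arm and a drop of 0.02 they are about 66% and 91%.

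**4. Power, harm confined to a minority.** Same control distribution and n.

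- 20% of babies lose 0.10 and the rest nothing, so the average drop is again 0.02. Share below 7.2 = 0.8×0.191 + 0.2×Φ(0.03/0.08) = 0.8×0.191 + 0.2×0.646 = 0.282. Proportions: 0.0911/0.0306 = 2.98, power about 85%.
- For the means, the SD in the affected arm becomes sqrt(0.08² + 0.2×0.8×0.10²) = 0.0894. SE = sqrt((0.0064 + 0.0080)/382) = 0.00614; 0.02/0.00614 = 3.26, power about 90%. Information lost by the cut: 1 − (2.98/3.26)² ≈ 16%.
- 10% of babies lose 0.12 (average drop 0.012): about 45% for the proportion and 51% for the means.

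In each case worked here the means do at least as well as the cut. The advantage is large under a uniform shift and small when harm is concentrated.

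**The case against.** The choice is defensible. A threshold counts babies with a low value, whereas a mean shift of 0.02 has no clinical meaning stated in the protocol. If compression harms only a vulnerable minority, the threshold loses little, as step 4 shows. That stands, and it is why the threshold should be kept.

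Four stronger readings are tempting, and the document does not support them.

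- *Cord pH is the only objective neonatal measure.* Neonatal death is also listed and is objective. Cord pH is the only laboratory measure.
- *Cord pH is the measure of the harm feared in the Background.* That section speaks of intracranial pressure, cerebral blood flow, brain damage and fractures. The listed outcomes that match it directly are encephalopathy and injury.
- *The plan throws away half the information.* That needs roughly 15-25% of babies below 7.2, plus normality and a uniform shift. The protocol supplies none of these.
- *The measured values will never be compared, or will be used to declare no fetal harm.* The wording of the continuous-variable rule is open, and the Data management section promises a separate analysis plan, not shown, which may add such an analysis. No non-inferiority or absence-of-harm claim on pH is planned.

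It is also not stated whether the case report form captures the numeric pH or only a category, so availability of the values cannot be taken for granted.

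What remains is that the outcome list, as published, fixes the endpoint in its less efficient form.

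**Conclusion.** The point holds as a suggestion for efficiency in a secondary safety outcome. It is not an error or an internal contradiction, and it does not touch the primary analysis. Under a roughly normal pH and a uniform shift, the cut costs at least 36% of the information at any prevalence, and more as values below 7.2 become rarer. If harm is concentrated in a minority, the cost is small: about 16% in the first such example. The power figures assume a mean of 7.27, an SD of 0.08 and a usable cord sample from every baby; missing samples would lower power for both analyses. Priority is low, but the improvement is worth making because it needs no additional women.

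**What to change.** - In Study outcomes, list cord blood pH as a continuous outcome as well, and keep pH below 7.2 beside it as the clinical threshold.
- Confirm that the case report form records the numeric pH, and amend it if it records only a category.
- Compare mean pH between arms with 95% intervals under the existing rule for continuous variables, and report the risk ratio for the threshold alongside.
- If the separate analysis plan already contains this comparison, bring the outcome list into line with it.

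Cost: one line in the outcome list, possibly one field on the form, and three more secondary comparisons, because Study objectives compares the three arms pairwise. No additional women are needed, and classifying a baby as below 7.2 already requires a measured value.
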